### Cortisol

Cortisol levels from hair and fingernail samples will be analysed to determine 1) whether maternal hair cortisol is significantly associated with infant neurocognitive outcomes (i.e., performance in task based fNIRS and EEG), 2) whether infant nail cortisol is a viable method of measuring infant cortisol soon after birth and 3) the stability of maternal hair cortisol levels pre- and post-birth. Furthermore, analyses will explore whether associations found for [1] are mediated by maternal mental state, pregnancy-related anxiety and birth-specific factors (delivery type, complications), and how maternal psychological stress accounts for variability in fetal behaviour and in offspring cortisol levels immediately following birth and the trajectory of cortisol in the subsequent months.

### Analyses and data availability

To study inter and intra-individual differences, analyses will involve approaches that allow assessment of the full cohort, as well as statistical models accounting for typical variation in available data to assess the contribution of early adversity/contextual risk factors to individual infant development. To maximise power, longitudinal multivariate analyses will make use of full information maximum likelihood setups that use both complete and partially complete data records, and where appropriate the multiple assessments of the same construct. Typical MANCOVA style testing will be undertaken in a generalised structural equation modelling framework (SEM/mixed models) suitable for (i) analysing both normally and non-normally distributed infant measures, (ii) the study of longitudinal and cross-sectional variation in testing age to fit growth curve models and (iii) comparison across different measures. Whenever possible, comparison data from previous cohorts will be included for combined or replication analyses.

The four study hypotheses will be addressed as follows:

*Hypothesis 1*: Inter-individual differences in basic sensory and motor processing are consistent between late prenatal and early postnatal periods.

This hypothesis will be tested by first assessing fetal movement in response to social and non-social habituation paradigms at 32 and 34 weeks gestation. We expect that at each gestational week, fetuses will react differently to social and non-social auditory stimuli (e.g., greater velocity of movement; displaying mimicry orofacial reactions to social auditory stimuli), with a decrease in arousal, movement velocity and an increase in habituation upon repeated exposure. Also, we expect to observe developmental changes in fetal auditory habituation rates between 32- and 34-weeks’ gestation due to maturation.

Second, we will investigate the relationship between these fetal habituation rates and postnatal habituation measures using data from the Neonatal Behavioural Assessment Scale (NBAS) and the fNIRS Habituation and Novelty Detection (HAND) oddball task which are carried out during the newborn period. Lastly, we will assess spontaneous rhythmical movements such as hand-to-mouth and arm movements, comparing baseline spontaneous movements pre-birth with post-birth measures recorded during NBAS and PCI.

Exploratory analysis of later postnatal outcome measures will also be conducted, to assess whether inter individual differences in fetal auditory habituation rates are related to observable differences in postnatal assessments at 3, 5 and 9 months.

*Hypothesis 2:* There is rapid change in cortical functions over the first postnatal days, particularly for brain networks that support social behaviour.

Hypothesis 2 will be assessed by determining change between brain function (NIRS) measurements during the first and second weeks, and at one month. Specifically, in accordance with the Interactive Specialisation model of emerging cortical functions [95] we will assess developmental trajectories of both the spatial specificity and magnitude of the observed cortical responses. For the *fNIRS Social/Non-social* task version (i) (visual only) we predict stronger haemodynamic responses to social dynamic stimuli vs non-social dynamic stimuli over posterior superior temporal sulcus and temporoparietal junction channels. For version (ii) (auditory only) we predict a more spatially restricted vocally selective (vocal > non-vocal) response over the anterior superior temporal gyrus and middle temporal gyrus channels during the neonatal period, which will become stronger with age. Furthermore, we predict more widespread spatially dispersed non-vocally selective response at the youngest ages which will specialise towards vocal selectivity across the first weeks and months of postnatal life [95]. For version (iii) (both visual and auditory) we expect both these effects.

For the fNIRS *Functional connectivity task* we expect intra hemispheric connectivity to be stronger than inter hemispheric and anterior-posterior connectivity during the first week(s) of life with a shift to more long-range connectivity as the infant becomes older. We will explore whether those infants with more rapid developmental trajectories of connectivity patterns associate with those showing more rapid social selectivity during the *fNIRS Social/Non-social* task.

We will also assess continuity and change in the social interaction and visual orienting measures from the Neonatal Behavioural Assessment Scale (NBAS) between newborn and 1-month timepoints, and assess how these behavioural responses correlate with the fNIRS measured brain responses.

Behavioural measures taken at later study timepoints such as eye tracking and Mullen (5 months), and Communication Development Inventory (CDI) and Vineland (9 months) will be used to assess whether differences in early brain development relate to observable differences in behaviour in subsequent months.

*Hypothesis 3:* Subsequent development in brain function is associated with experience of social interaction with other humans.

Hypothesis 3 will be assessed by initially determining changes in brain function (NIRS) measurements between one month and at five months, again assessing developmental trajectories of both the spatial specificity and magnitude of the observed cortical responses [95].

Similarly, we will use EEG data collected at 1 and 5 months to examine developmental changes in emerging spatial and temporal specificity of activation in response to auditory stimuli, and will also assess how this relates to individual differences in sensory processing.

Furthermore, these measures of brain function will also be related to measures of social experience to assess how experience of social interactions influences the emergence of frontal and temporal cortical social brain function [94]. Measures of social experience include the ‘face-time index’ calculated from the baby head-camera footage during the home recording visit at 3 months, the amount of language the infant is exposed to in a typical day (as recorded by the LENA recorder during the home recording visit), caregiving practices (recorded via questionnaires), and measures of parent sensitivity and responsivity coded from the Parent-Child Interaction videos at 1 and 5 months.

*Hypothesis 4:* Individual differences in developmental trajectories associate with low resource (poverty) associated risk factors.

We aimed to recruit participants from diverse backgrounds, particularly from less affluent areas and rural settings (i.e., those less likely to participate in research). The questionnaires that parents complete throughout the study will give us a rich understanding of each child’s home environment, including factors associated with low-resource settings such as parental education levels, family income, multiple deprivation index of home postcode, organisation of home life, social and family support, and mental health and wellbeing. These measures will allow us to investigate differences in the measures and analyses described above that relate to early exposure to poverty.

Furthermore, we will assess whether physiological factors relating to stress, such as higher mean heart rate, lower heart rate variability and higher levels of cortisol vary between infants from high- and low-resource families.

Upon completion of data curation, details of data availability will be published on our Open Science Framework page.

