## Introduction

### Background & rationale

Birth represents the most significant environmental change that a brain experiences in its lifetime [1,2], and triggers a period of rapid growth and development, making the late prenatal and the early postnatal period a critical time for identifying early-stage markers of later outcomes. While the immediate postnatal period has been little studied, recent evidence supports its importance as: (a) interneurons are still migrating to the prefrontal cortex [3]; (b) initial studies indicate rapid change in brain function over the first days post-birth [4]; and (c) brain development atypicalities can first emerge during the first six months of life [5,6].

Preparation for this new world outside of the womb begins during pregnancy [7], and recent advances in 4D ultrasound technology have allowed researchers to measure fetal behaviour and development from the second trimester onwards [8,9], allowing for the assessment of transnatal sensory continuity from pre-to-postnatal life [10,11]. From the end of the second trimester, when fetal sensory systems are developed and fetuses can sense, distinguish, and react to various stimuli such as touch, taste, smell, light, and sound [12], measurements of fetal behaviours in response to sensory stimuli and assessment of fetal learning and memory through habituation [13–16] are possible.

Relatively little is known about the rapid period of development in the first weeks and months after birth, partly due to this window of development coinciding with a challenging time for families to travel and participate in research outside of their community and home. Therefore, it is critical that we find better ways to bring research to homes and communities rather than expecting families to come to us. Furthermore, sampling in the home allows us to unravel developmental effects associated with the child’s environment. Advances in portable/wireless functional Near Infrared Spectroscopy (fNIRS) and electroencephalography (EEG) technology mean that there are now suitable and reliable ways to study brain structure and function in newborns, allowing for the investigation of rapid postnatal brain specialisation through repeated testing of infant cortical responses from birth, while the miniaturisation of audio-visual and physiological recording devices allows naturalistic recordings of an infant’s everyday experiences at home.

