### Study design

PIPKIN participants attend study visits at seven timepoints as shown in Fig 1. Families were consulted on all aspects of the research during the piloting phase and protocols were adjusted in response to parent feedback.

Written ethical approval for the study was obtained from Cambridge Psychology Research Ethics Committee (Application no. PRE.2020.123) and the East Midlands – Nottingham 1 NHS Research Ethics Committee (REC reference 22/EM/0004, IRAS project ID: 295027).

Further details of measures taken across timepoints are given in Table 3 and elaborated below. Further details of each paradigm will be added to the Open Science Framework PIPKIN protocol paper page.

**Table 3 pone.0330915.t003:** Summary of the PIPKIN protocol.

	Antenatal		Postnatal							
Ultrasound measures	32 wks	34 wks	0-7 days	7-14 days	1 mo	2 mo	3 mo	4 mo	5 mo	9 mo
**Fetal biometric measures**	**x**	**x**								
**Spontaneous (baseline) movements**	**x**	**x**								
**Social/Non-social auditory habituation task**	**x**	**x**								
**Neuroimaging measures**	**32 wks**	**34 wks**	**0-7 days**	**7-14 days**	**1 mo**	**2 mo**	**3 mo**	**4 mo**	**5 mo**	**9 mo**
**fNIRS: Social/Non-social visual only (awake)^**			**x**	**x**	**x**					
**fNIRS: Social/Non-social auditory only (asleep)**			**x**	**x**	**x**					
**fNIRS: Social/Non-social visual and auditory (awake)**									**x**	
**fNIRS: Habituation and novelty detection (HAND) (asleep, awake at 5mths)**			**x**	**x**	**x**				**x**	
**fNIRS: Task-free functional connectivity (asleep)**			**x**	**x**	**x**					
**fNIRS: Functional connectivity (awake)**									**x**	
**EEG: Auditory Oddball Habituation (asleep)**					**x**				**x**	
**EEG: Resting state (asleep)**					**x**				**x**	
**EEG: Gaze ERP task (awake)**									**x**	
**Behavioural/Neurocognitive measures**	**32 wks**	**34 wks**	**0-7 days**	**7-14 days**	**1 mo**	**2 mo**	**3 mo**	**4 mo**	**5 mo**	**9 mo**
**Neonatal Behavioural Assessment Scale (NBAS)**			**x**	**x**	**x**					
**Parent-Child Interaction video (PCI)**					**x**				**x**	
**Mullen Scales of Early Learning (MSEL)**									**x**	
**Eye-tracking: Gap/Overlap (disengagement)**									**x**	
**Eye-tracking: Non-social contingency**									**x**	
**Eye-tracking: Fifty faces**									**x**	
**Eye-tracking: Dancing ladies**									**x**	

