### Ultrasound measures

In the last trimester of pregnancy, antenatal scans are recorded at 32- and 34-weeks gestation using a GE Voluson E10 ultrasound machine, equipped with the GE eM6C matrix electronic 4D probe, at the Rosie Maternity Hospital in Cambridge. During this session, the sonographer first completes fetal anthropometric measures such as heartbeat, Abdominal Circumference (AC), Head Circumference (HC), and Amniotic fluid index (AFI). Then 4D scans record spontaneous baseline movements without any stimuli presentation for approximately five minutes. Next, fetal movements are recorded during the presentation of an auditory habituation paradigm that includes social sound stimuli (‘MA’ and ‘MO’) based on the design by Reissland et al. [13], and pink noise (PN) as a non-social sound stimulus. For each sound stimulus, 1-minute blocks of duplicate presentations by a female voice are played, including identical presentations of the stimuli for 0.4 seconds (+0.8 second silence), with a 5 second silent interval between the blocks. The order of the sound stimuli is counterbalanced and presented in one of the following sequences: ‘MA, PN, MO, PN, MA, MO’, or ‘MO, PN, MA, PN, MO, MA’. The sound stimuli are delivered through speakers placed approximately 60 cm from the mother’s abdomen. The auditory stimuli, containing frequencies between 0.6 Hz and 3.6 kHz, are presented at average decibel levels ranging from 47.6 dB to 54.07 dB, audible to fetuses from 29 weeks of gestational age [47,48].

During the 4D ultrasound scanning (Fig 2), we record the fetal face and upper torso (at 24 frames per second), which is later coded offline for fetal movements using an established and reliable coding system for fetal movements [49]. The entire ultrasound procedure takes approximately 30–40 minutes to complete of which 10–15 minutes are dedicated to 4D ultrasound scanning (baseline + in response to habituation paradigm). Both mother and partner (or additional family member) are present in the ultrasound room and are able to watch the fetus via a monitor. The session is adapted to the mother’s needs to ensure she is comfortable throughout. The individuals pictured in Fig 2 have provided written informed consent (as outlined in PLOS consent form) to publish their image.

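### The 32-to-34-week change in fetal habituation cannot be put down to maturation, because every 34-week scan is also a second exposure to the same sounds

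*Protocol article*

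**What the plan says.** All places are in the protocol article.

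- **Timing.** Ultrasound measures (Methods): "antenatal scans are recorded at 32- and 34-weeks gestation". No visit window is given.
- **Task.** In Table 3 (Study design) the row "Social/Non-social auditory habituation task" is marked at both antenatal visits. The Hypothesis 1 text under Analyses and data availability tests it at both ages: "first assessing fetal movement in response to social and non-social habituation paradigms at 32 and 34 weeks gestation".
- **Stimuli.** Ultrasound measures describes one set: two spoken syllables (MA and MO) and pink noise. No alternative set is described for the second scan.
- **Counterbalancing.** "The order of the sound stimuli is counterbalanced and presented in one of the following sequences". Each of the two sequences contains MA twice, MO twice and pink noise twice.
- **Inference.** "Also, we expect to observe developmental changes in fetal auditory habituation rates between 32- and 34-weeks’ gestation due to maturation". No direction of change is given.
- **Later use.** "we will investigate the relationship between these fetal habituation rates and postnatal habituation measures", the postnatal measures being the NBAS and the fNIRS habituation and novelty task. The text does not say how the two scans' rates enter that analysis.
- **Background.** Background & rationale lists as feasible "measurements of fetal behaviours in response to sensory stimuli and assessment of fetal learning and memory through habituation".

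**The concern.** A change from 32 to 34 weeks is given a cause in advance, but on the schedule each fetus is both two weeks older and no longer new to the sounds at the second scan. The article itself regards habituation as a way to study fetal learning and memory. A study using the task in that way should not assume without comment that a second session with identical sounds is untouched by the first.

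At stake is one conclusion: that fetal auditory habituation develops between 32 and 34 weeks. Because no direction is predicted, any difference between the scans would appear to confirm it, including one produced entirely by earlier exposure.

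**Working it through.** The article gives no figure for this contrast, so there is none to reproduce. The check is whether the effect can be identified.

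**1. Exposure at the first scan.** Ultrasound measures gives one-minute blocks, 0.4 s of sound plus 0.8 s of silence per presentation, and six blocks.
- Presentations per block: 60 / (0.4 + 0.8) = 50.
- Per session: 6 × 50 = 300. Per sound: 2 × 50 = 100.

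So the 34-week scan follows about 100 presentations of each sound. This shows that prior exposure is substantial. It does not show that it is retained.

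**2. The within-fetus difference.** Let m be the weekly maturation effect and c the carry-over from the first session. Then

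E[rate at 34 weeks − rate at 32 weeks] = 2m + c.

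There is one observable quantity and two unknowns. If m = 0, any non-zero c still appears as a change. If m and c have opposite signs, they can cancel.

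**3. Rank of the design.** Code exposure as 0 for the first session and 1 for the second. At the scheduled ages, age = 32 + 2 × exposure for every scan. The columns intercept, age and exposure therefore have rank 2 of 3. Adding stimulus sequence gives rank 3 of 4, whether a fetus keeps its sequence or switches between scans. Counterbalancing the order of sounds does not break the alias, and neither does a larger sample.

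**4. Would spread in actual scan dates help?** The article gives no spread, so assume that scan age varies around 32 and 34 weeks with standard deviation s, in weeks. Pool all scans and ignore the pairing within fetus. Half the scans are at each nominal age, so the variance of age explained by exposure is 2² × 0.25 = 1. The squared correlation is then 1 / (1 + s²), and the variance inflation factor is 1 / (1 − r²) = 1 + 1/s².

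| Assumed s (weeks) | Correlation | Variance inflation | Standard error multiplied by |
|---|---|---|---|
| 0.1 | 0.995 | 101 | about 10 |
| 0.2 | 0.98 | 26 | about 5 |
| 0.3 | 0.96 | 12 | about 3.5 |
| 0.5 | 0.89 | 5 | about 2.2 |

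Unplanned spread makes separation possible in principle but weak. A growth curve with no exposure term would credit c to age.

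**5. Effect on the prenatal-to-postnatal analysis.** Let R be the 34-week rate without carry-over and P a postnatal measure. If c is the same for every fetus, corr(R + c, P) = corr(R, P): the mean shifts but the association does not. Only carry-over that differs between fetuses could alter it, and the article gives no information on that.

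**The case against.** The strongest reply is that the sentence is an expectation, not a result; that it is one sub-prediction within Hypothesis 1; and that nothing in the article says a fetus retains these sounds for two weeks. The predicted rise in habituation with repeated exposure is framed for each gestational week, so it most naturally means repetition within a session. All of this stands. It limits what can be said about the size of any bias, but it does not make the attribution to maturation identifiable.

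A second reply points to the planned growth curves using variation in testing age, the use of partially complete records, and comparison data from previous cohorts. These statements are general. None is tied to the fetal task, and no cohort first exposed at 34 weeks is named. An exposure term could be specified within that framework, but the framework alone does not break the alias.

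A reader might also infer that the Hypothesis 1 consistency analysis treats the two scans' rates as interchangeable and is therefore compromised. The article does not support that. It does not say the rates are pooled, its preceding sentence expects them to differ, and a carry-over common to all fetuses would leave between-fetus associations unchanged. Nor does it support a percentage by which maturation would be overstated: any such figure only restates an assumed carry-over.

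**Conclusion.** The concern holds for one inference. On the published schedule, gestational age and exposure number have correlation 1, so the 32-to-34-week change in habituation rate cannot be assigned to maturation. This rests on the schedule being followed as written. Fetuses who missed the 32-week scan, or real spread in scan dates, would allow weak separation, but the article reports neither.

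The size of any bias is unknown and could be zero. The within-scan contrast of social and non-social sounds is unaffected. The consistency test at the centre of Hypothesis 1 is not shown to be harmed. Using only the first scan as the main fetal marker is not warranted: it would set aside half the scheduled fetal measurements to guard against an effect that may not exist. This is a modest point about what the study may conclude.

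**What to change.** 1. Under Hypothesis 1, replace the attribution to maturation with wording such as: *change between the first (32-week) and second (34-week) exposure, reflecting maturation, prior exposure or both*. Draw no maturation conclusion from this contrast alone.
2. As a supporting analysis only, and where the data allow, estimate the age effect from first exposures: the spread of exact gestational age at the first scan, plus any fetuses first tested at about 34 weeks. State in advance that the estimate will be imprecise. This assumes that exact gestational age and session number are held for each scan, which the article does not state.
3. In the prenatal-to-postnatal analysis keep both scans, and also report the associations separately for the 32-week (first-exposure) and 34-week (second-exposure) rates.

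No visit, stimulus or procedure changes, so this is feasible although recruitment is nearly complete. The cost is a weaker developmental claim and a little extra analysis and reporting.

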## Conclusions

The PIPKIN study is a comprehensive and multi-method study of development during pregnancy and the first 9 months of postnatal life in the UK, with a particular focus on the perinatal transition from pre- to post-natal life. The combination of neuroimaging, behavioural, parent-report measures, and biological samples provides a unique opportunity to study a variety of context-associated moderators which may or may not be related to poverty, the social environment and family context, as well as the mechanistic processes underlying associations between markers and outcomes. On one hand, we hope that our work will be an asset to the study of neurocognitive development in early infancy, particularly the use of still emergent neuroimaging tools. On the other hand, this work has broader value for developmental research in general. Due to the logistical and financial constraints of longitudinal research, our project is among the few to assess early development across a large number of study visits starting during pregnancy, and to incorporate such a variety of methods. Thus, the generated results will enable us to identify critical windows for developmental vulnerability and act as rationale to guide future interventions which aim to protect and enrich the developing brain within contexts associated with risk. We propose that our project provides a roadmap for other researchers interested in conducting studies of neurocognitive development in more naturalistic home environments with similar contextual factors.
